#### Print-based intervention arm

Participants in the print-based group received a hard copy booklet that provided the same educational materials and ManUp challenges as those received by participants in the IT-based intervention. Participants in the print-based group were not provided with information on their peers in this group. The print-based booklet also included log sheets that could be used to monitor their progress and/or successful completion of any of the ManUp physical activity or healthy eating challenges.

#### Measures

All participants completed an online questionnaire at baseline and completed follow-up online questionnaires at 3 months and 9 months after they began the intervention. A randomly selected sub-sample (n = 91, 61 from IT-based intervention arm, 30 from print-based intervention arm) of participants also attended one of the trial centres (CQUniversity Gladstone or Rockhampton Campus) for an in-person assessment at each time point. During in-person assessments, participants completed the online survey, received an accelerometer for the objective measurement of physical activity, and had their height, weight and waist circumference measured by a trained research assistant.

#### Demographic characteristics

Participants self-reported the following demographic characteristics: age, employment status, level of employment, industry of employment, number of hours of work per week, household income, years of education, number of children (aged <18 years) living in the household, living situation, and presence of any chronic diseases diagnosed by a doctor.

#### Perceived health status

Participants reported on several aspects of perceived health status that have been identified as risk factors for health behaviours and chronic disease
[16,33]. Two items were used to assess risk perception in relation to physical activity and body weight, consistent with previous research
[16]. The items are “I believe that I am doing enough exercise/physical activity to achieve health benefits” and “I believe that my current body weight is a risk to my health.” Responses were measured on a five-point Likert type scale from strongly agree to strongly disagree
[16]. The self-rated health item from the Healthy Days Module of the Behavioral Risk Factor Surveillance Survey (BRFSS) was used to assess self-rated health, and response options were excellent, very good, good, fair or poor
[34].

#### Weight

All participants self-reported current height (cm), weight (kg), and waist circumference (cm) during the online survey. For those individuals selected for in-person assessments, these measures are also measured by project staff. During in-person assessments, participant height to the nearest 0.1 cm (PE087, Mentone Educational, Victoria, Australia), weight to the nearest 0.1 kg (Tanita BF-681, Tanita Corp., Tokyo, Japan) and waist circumference to the nearest 0.1 cm (Lufkin Executive W606PM) are measured at each assessment point, in triplicate. Participants are asked to wear light clothing and to remove shoes prior to the assessment. Waist circumference is measured horizontally at the umbilicus, after normal expiration, by a trained research assistant.

#### Activity related behaviours

Physical activity was assessed in all participants using the Active Australia Questionnaire, which assesses the frequency and duration of transport and recreational walking, moderate and vigorous intensity physical activity
[35]. The Active Australia Questionnaire has demonstrated acceptable levels of test re-test reliability and validity in the Australian adult population, and has been identified as a useful measure to detect intervention-related change in physical activity behaviours
[36-39]. Participants (n=91) who selected to attend in-person measurement sessions were fitted with an ActiGraph GT3X (ActiGraph, Pensacola, FL) accelerometer to provide objective measures of activity behaviours over a five-day period. Participants were instructed to wear the ActiGraph, mounted on an elastic belt around the waist with the unit positioned over the right hip during all waking, non-contact activities (thus excluding activities like rugby league or rugby union) and non-water-based activities. The ActiGraph monitors were set to record steps, inclination, and acceleration counts in tri-axial mode, using a 10-second epoch. Accelerometer data was analysed using the MeterPlus program
[40] in 10 second epochs using previously reported cut-points for sedentary, light and moderate-to-vigorous intensity physical activity
[41]. Non wear time was assessed using a minimum of 60 minutes of consecutive zero counts allowing up to a 2 minute tolerance of non-zero counts. A minimum of 10 hours per day of wear time on at least four days was required to be included in analysis.

Self-reported duration of sitting in occupational settings over the previous seven days was assessed using two items. Adapted from an existing measure of occupational sitting
[5,42], the first item asked participants to report the amount of time sitting at work during meetings, lunch and at their desk. Using the same recall period the second item asked participants to report the amount of time spent driving at work. Both items asked participants to report the duration of sitting in hours and minutes. Duration of sitting in leisure time was assessed using items adapted from a existing measure of nine leisure-time sedentary behaviours with demonstrated acceptable test-retest reliability
[43]. The sedentary behaviours that were assessed included computer use, hobbies, television viewing, sitting and socializing, reading, sitting or lying down while listening to music, talking on the telephone, going for a recreational drive, and relaxing, thinking and resting
[43]. These items were modified to explicitly ask about time spent sitting while performing each behaviour, instead of time spent engaged in each behaviour.

#### Nutrition behaviours

Nutrition behaviours related to the healthy eating guidelines for Australian adults
[32] were assessed using 19 items adapted from the National Health Survey Australia and the Monitoring Food Habits Questionnaire
[44,45]. The number of daily serves of fruit and vegetables usually consumed in the previous week was assessed using two separate items, based on those used in the National Health Survey
[44]; possible response options were: one serve or less; two to three serves; four to five serves; six or more; and don’t consume this food. The number of times in the previous week that red meat, fish, meat products (sausages, salami, meat pies, etc.), cooked cereals, bread, soft drink, chips, takeaway foods, and sweet or savoury foods were consumed was assessed using a nine-point scale from rarely/never to more than seven times per week, each item also included a “don’t consume this food” response option. The volume of milk consumed each day and the type of milk (whole milk, reduced fat, soy milk, condensed milk) was assessed using two separate items
[44].

#### Health literacy

Health literacy can be defined as the acquisition of a set of skills and knowledge that can be applied to change behaviours and improve health
[22,46]. The five physical activity awareness items from the Active Australia Questionnaire were used to assess health literacy related to physical activity
[35]. These items assess awareness related to the health benefits of physical activity that include the minimum amount of physical activity required for health benefit, the appropriate intensity of physical activity to achieve benefit, and the pattern in which physical activity can be accumulated to receive health benefits
[35]. The 28-item Nutritional Literacy Survey was used to assess health literacy related to healthy eating
[47]. This instrument presents sentences to the respondent that contain one or more words removed from the sentence, the respondent is provided with four possible response options and asked to select the response that best fits the sentence
[47]. Topics covered include food types that promote heart health, fat and cholesterol contents of food, and portion size
[47].

#### IT platform usage

Both the website and mobile platforms allow monitoring of the number of times a participant has logged in, the number and date of entries made, and the number of challenges created and completed. The website platform also permits monitoring of which educational resource pages have been viewed by participants. These measures describe the level of participant engagement with the intervention components.

#### Sample size

The study was powered to detect a 60-minute increase in moderate-to-vigorous intensity physical activity using a 0.05 alpha, with a power level of 90%. Based on these factors, it was estimated that 197 participants would be required
[48]. Typical dropout rates in IT based interventions are approximately 30%
[16]. Given the difficulty in engaging and retaining the target population (middle aged males) the estimated sample size was increased to account for a 45% dropout rate. Methods described by Hsieh to account for the loss of power associated with the 2:1 group allocation
[49], the estimated sample size was further inflated using a variance inflation factor of (VIF = 1.125) resulting in a total estimated sample size of 321; 107 allocated to the print-based group and 214 allocated to the IT-based group.

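### The stated 90% power for a 60-minute gain does not fit the article's own baseline spread: if total weekly activity is the outcome, power is about 19% to 68%

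*Protocol article*

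**What the plan says.** The Sample size section sets the target in one sentence: "The study was powered to detect a 60-minute increase in moderate-to-vigorous intensity physical activity using a 0.05 alpha, with a power level of 90" (per cent). The number before any inflation is credited to a cited source: "it was estimated that 197 participants would be required". An allowance for loss comes next: "the estimated sample size was increased to account for a 45% dropout rate". The 2:1 allocation is then handled by a further factor of 1.125, and the chain ends at 321 in all, 107 print and 214 IT. No SD, standardised effect, sidedness or time unit for the 60 minutes is given.

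The section on activity-related behaviours says which instrument covers everyone: "Physical activity was assessed in all participants using the Active Australia Questionnaire". That questionnaire counts walking as well as moderate and vigorous activity. The accelerometer was worn only in a sub-sample of 91, of whom 77 (25 print, 52 IT) had valid baseline data.

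Table 4 reports weekly minutes of physical activity as mean (SE): 277.9 (34.0) in 96 print participants and 286.1 (23.3) in 205 IT participants. The article does not return to the power statement after presenting these data.

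**The concern.** A sample size for a difference in means rests on an SD. Here the SD is not printed, but the 60 minutes, the 90% and the 197 fix it once a design is assumed, and the article also publishes baseline data from which the actual spread can be recovered. If the actual spread is much larger than the planning value, the trial does not have the power it claims for its own target difference. A true 60-minute advantage of the IT arm could then easily be missed, and a reader of the results who trusts the 90% would give a non-significant finding too much weight.

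**Working it through.** **1. Reproduce the plan's chain.** 197 × 1.45 × 1.125 = 321.4, which matches 321. The 2:1 factor is 1/(4 × 1/3 × 2/3) = 1.125. Because this factor is applied to 197 and the product is called a total, 197 reads most naturally as a two-group total at equal allocation. The 197 itself cannot be reproduced forward, since no SD is stated.

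**2. SD implied by 197.** With z = 1.960 + 1.2816 = 3.2415 (two-sided 0.05, 90% power), the detectable standardised difference is 3.2415 × √(4/197) = 0.462, so SD = 60/0.462 = 129.9 minutes. Other two-group readings:
- one-sided, 197 in total: 143.9
- two-sided, 197 per arm: 183.7
- one-sided, 197 per arm: 203.5

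**3. SD observed at baseline (Table 4).** Print: 34.0 × √96 = 333.1. IT: 23.3 × √205 = 333.6. The ratio of the SEs, 34.0/23.3 = 1.459, is almost exactly √(205/96) = 1.461. The two SEs therefore appear to come from one pooled model variance, and I count 333.4 as a single estimate. It is 333.4/129.9 = 2.6 times the value in step 2, and 1.6 times the largest alternative (333.4/203.5).

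**4. Power for 60 minutes a week, between arms.** SE = 333.4 × √(1 − r²) × √(1/n₁ + 1/n₂), and power = Φ(60/SE − 1.96), where r is the baseline-to-follow-up correlation used in adjustment. The article does not give r; I take 0 to 0.8. The numbers analysed are:
- A: the 301 with baseline data, less 45%: 112.75 and 52.8, root term 0.1668
- B: the 317 randomised, less 30% (the article's typical dropout), split 2:1: 147.9 and 74.0, root term 0.1424
- C: all 301, no loss: 205 and 96, root term 0.1237

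| r | A: power | B: power | C: power |
|---|---|---|---|
| 0 | 19% | 24% | 31% |
| 0.5 | 24% | 31% | 39% |
| 0.7 | 33% | 42% | 53% |
| 0.8 | 44% | 56% | 68% |

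Example (A, r = 0): SE = 333.4 × 0.1668 = 55.6; 60/55.6 − 1.96 = −0.88; Φ(−0.88) = 0.19.

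**5. Difference detectable with 90% power** = 3.2415 × SE, in minutes per week:

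| r | A | C |
|---|---|---|
| 0 | 180 | 134 |
| 0.5 | 156 | 116 |
| 0.7 | 129 | 95 |
| 0.8 | 108 | 80 |

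**6. What would rescue the claim.** Adjustment would have to cut the SD from 333.4 to 129.9, which needs r = √(1 − (129.9/333.4)²) = 0.92. At r = 0.9, scenario A gives 70%; only the no-loss scenario C passes 90% (92%).

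**The case against.** **The SD of 130 is inferred.** The article states no SD and takes 197 from a source that is not shown. A reader might infer that the sample size calculation is arithmetically wrong; the document does not support that, because its SD is unknown and the step from 197 to 321 reproduces. The wording about an increase even allows a single-group, before-after reading: 197 would then need a change SD of 60 × √197/3.2415 = 260, which an SD of 333.4 gives at r of about 0.70. The 2:1 adjustment tells against that reading, because it belongs to a comparison of two arms.

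**The outcome may not be the Table 4 row.** The target names moderate-to-vigorous activity; the row is total activity including walking. It is tempting to say that 197 must refer to this row because only the questionnaire was given to everyone. That is an inference, and a self-report measure without walking could have a smaller SD. This objection stands as a limit on the result. For illustration, the accelerometer SDs are 4.9 × √25 = 24.5 and 3.2 × √52 = 23.1 minutes a day, or about 165 a week pooled. At that SD, the 177 completers expected from 321 (321 × 0.55) would have about 62% power unadjusted and 89% at r = 0.7. However, only 77 men had valid accelerometer data, for about 32% unadjusted.

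**The dropout scenario matters.** The 45% was a cautious allowance, and applying it to the 301 counts some early loss twice, since 16 men had already left after randomisation. Quoting only scenario A would be selective, so B and C are shown too.

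**Mixed models use both follow-ups.** If the effect is averaged over 3 and 9 months, with the same r between all time points, the residual variance factor is (1 + r)/2 − r². Scenario A then gives 34% at r = 0.5 and 44% at r = 0.7, and scenario C gives 54% and 68%. At r = 0.8 with no loss it reaches 81%. This helps but does not restore 90%.

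**Skewness.** An SD above the mean indicates strong skew, and baseline SD stands in for follow-up SD. The power figures are approximate.

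**Conclusion.** The concern holds in conditional form. If the 60 minutes are per week, the contrast is between arms, and the outcome is total self-reported activity or something equally variable, the design has about 19–44% power with 301 men and 45% dropout, 24–56% with 30% dropout from 317, and 31–68% with no loss (r = 0 to 0.8, single follow-up). All are well below 90%, and a 2.6-fold gap in SD is too large for skewness or rounding to explain. Even the most generous two-group reading of 197 implies an SD of 204, far below 333.

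The article does not establish that the authors assumed 130, that Table 4 confirms 333 twice, or that the outcome was certainly total activity. A reader might also infer that a null result will be reported as showing the two arms equal; nothing in the article plans that. The point is that an unqualified 90% stands beside baseline data that do not support it.

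**What to change.** In the Sample size section, keep 197 and 321 as the historical planning figures, and name the outcome and time unit to which they refer. Replace the unqualified 90% claim with the difference detectable at 90% power from the observed baseline SD, giving the assumed correlation and dropout. On the Table 4 row this is 180, 156, 129 and 108 minutes a week at r = 0, 0.5, 0.7 and 0.8 with 301 men and 45% dropout, and 134 down to 80 with no loss. If the intended outcome excludes walking, use the baseline SD of that measure instead.

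This needs text and baseline data already in hand, and no look at follow-up outcomes by arm. The cost is that the stated power becomes less favourable.

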### Participants, recruitment and group allocation

Eligible participants were males aged 35 to 54 years old who (1) owned a mobile telephone, (2) had access to the internet, (3) did not have a mobility impairment, (4) resided in the cities of Gladstone or Rockhampton (Queensland, Australia), and (5) were classified as low risk to commence an exercise regime
[26]. Participants (n = 317) were recruited using a variety of techniques including advertisements via local newspapers, trading magazines, face-to-face information sessions with local businesses, and distribution of leaflets and posters to local businesses, medical clinics, and offices of allied health professionals. Rolling participant recruitment occurred from October 2010 to September 2011. Following initial screening for inclusion criteria, participants were randomly allocated to an intervention arm. Group assignment was conducted on a two-to-one ratio in favour of the IT-based intervention arm. Unequal group allocation was conducted to maximize the number of participants allocated to the intervention arm that is less frequently examined in male populations
[19]. Randomization lists were generated using freely available software (
http://www.randomization.com). Participants were blinded to group allocation until baseline assessments were completed.

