#### Baseline characteristics of the sample

A total of 327 males contacted the research team about participation in the study, 10 males withdrew from the study prior to randomization to an intervention arm (Figure 
1). The primary reason for not continuing participation in the study was being no longer interested in participation after having details of the study explained to them. Following allocation to an intervention arm, nine participants in the IT-based intervention arm and seven participants in the print-based intervention arm did not complete a baseline assessment and were withdrawn from the trial (Figure 
1). Participants were asked how they learned about the existence of the ManUp project (for which they could report multiple methods); responses were classified into the following categories 1) project specific advertisements and promotional materials (n = 152), 2) word of mouth (n = 87), 3) information provided at their workplace (n = 75), 4) direct contact with project staff (n = 49), and 5) not specified (n = 1).

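### The total of 321 does not cover 45% dropout: it matches 197 × 1.45 × 1.125, and at 45% loss power is about 82%, not 90%

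*Protocol article*

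**What the plan says.** All of this stands in the Sample size section of the protocol article. The trial was "powered to detect a 60-minute increase in moderate-to-vigorous intensity physical activity", and on the stated alpha of 0.05 and power of 90% "it was estimated that 197 participants would be required". The section cites about 30% as the usual dropout in IT-based interventions. It judges that middle-aged men are harder to retain, and so "the estimated sample size was increased to account for a 45% dropout rate". A variance inflation factor of 1.125 is then applied for the unequal allocation, "resulting in a total estimated sample size of 321; 107 allocated to the print-based group and 214 allocated to the IT-based group".

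The dropout formula, the outcome SD and the sidedness of the test are not given.

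Two later counts bear on the size of the problem. The section on participants, recruitment and group allocation reports 317 men. The section on baseline characteristics says that nine men in the IT arm and seven in the print arm "did not complete a baseline assessment and were withdrawn from the trial", which leaves 301.

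**The concern.** A sample that must survive a loss of a fraction d has to be divided by 1 − d. Multiplying it by 1 + d gives too small a number, and the gap widens as d grows. At 45% the two factors are 1.818 and 1.45.

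The printed chain of 197, 45%, 1.125 and 321 fits the second rule and not the first. If so, the claim of 90% power after 45% attrition describes a property that the design does not have. This is the only power statement in the article. A non-significant comparison of the IT and print arms would be read against it, and type II error would be taken as 10% when it is nearer 18% at the planned dropout.

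**Working it through.** **Inputs** (protocol article, Sample size, unless noted)
- Required number before inflation: 197. It is read as the total under 1:1 allocation, because the 2:1 factor is applied afterwards.
- Alpha 0.05, taken as two-sided (an assumption); power 90%; dropout 45%.
- Allocation 2:1, with a factor of 1.125.
- Randomised: 317 (Participants, recruitment and group allocation). With baseline data: 317 − 9 − 7 = 301 (Baseline characteristics of the sample).

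**1. The allocation factor.** For 2:1, 1 / (4 × 1/3 × 2/3) = 1.125. This is correct, so the fault lies in the dropout step.

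**2. Reproducing the plan's figure.**
- Multiplying: 197 × 1.45 = 285.65, and 285.65 × 1.125 = 321.36. This matches 321.
- Dividing: 197 / 0.55 = 358.2, and 358.2 × 1.125 = 402.95, so 403. This does not match.
- Dividing for 30% dropout: 197 / 0.70 × 1.125 = 316.6. This is close to 321 but does not match it, and the text says 45%.

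**3. Completers needed and obtained.**
- Needed at 2:1: 197 × 1.125 = 221.6.
- Obtained from 321 after 45% loss: 321 × 0.55 = 176.6, equivalent to 176.6 / 1.125 = 156.9 men at 1:1, against 197.
- Shortfall in men randomised: 403 − 321 = 82.

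**4. Power at 45% dropout.** The unstated SD cancels, because the standardised effect is fixed by 197 men giving 90% power:

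Power = Φ((1.960 + 1.2816) × √(n_eff / 197) − 1.960), with n_eff = N × 0.55 / 1.125.

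| N before the 45% loss | Completers | n_eff | Power |
|---|---|---|---|
| 321 (planned) | 176.6 | 156.9 | 82.5% |
| 317 (randomised) | 174.4 | 155.0 | 82.0% |
| 301 (a further 45% lost after baseline) | 165.6 | 147.2 | 80.0% |
| 403 (needed) | 221.7 | 197.0 | 90.0% |

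For 321, a noncentral t calculation gives 82.4%, and a one-sided test at 0.05 gives 83.3%. The result does not depend on these choices.

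**5. Dropout at which 90% power is still kept.**
- 321: 1 − 221.6 / 321 = 31%.
- 317: 1 − 221.6 / 317 = 30%.
- 301, counting losses after baseline only: 1 − 221.6 / 301 = 26%.

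**6. Difference detectable with 90% power at 45% dropout.** 60 × √(197 / n_eff) gives 67.2 minutes for 321, 67.6 for 317 and 69.4 for 301, against the stated 60.

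**The case against.** Five points can be made on the other side.

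- **The formula is not printed.** Multiplication by 1.45 is an inference. This is true, but the contradiction does not rest on it: however 321 was reached, 55% of it is 176.6 men, fewer than the 221.6 needed and fewer even than the uninflated 197.
- **The 301 case counts early losses twice.** The 16 men withdrawn before baseline can be seen as part of the 45%. Taking a further 45% from 301 leaves 165.6 men, a loss of 1 − 165.6 / 317 = 47.8% of those randomised. This stands as a matter of labelling. The 80% and 26% figures, and the top of the 67 to 69 minute range, apply only if 45% are lost after baseline. The main result uses 321 or 317.
- **Mixed models use partial data.** The Analysis section plans linear mixed models and generalised estimating equations across time points, so a man lost after 3 months still contributes something. This is fair, and the 82% is therefore approximate. The Sample size section takes no credit for it, however, and a man lost before any follow-up adds little to the comparison of change.
- **At the cited 30% dropout the design is adequate.** Then 321 leaves 224.7 completers and 317 leaves 221.9, both above 221.6. This is correct, but the authors chose 45% because they thought 30% too optimistic for these men.
- **Recruitment is over and no analysis changes.** This also stands. No estimate, test or type I error is affected, so the matter is a reporting correction.

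**Conclusion.** The concern holds. The stated inputs and the stated total do not agree: 45% dropout needs 403 men, not 321. At that dropout, power is about 82% with either the 321 planned or the 317 randomised, and 80% if a further 45% are lost after baseline from the 301. The total of 321 protects 90% power only to 31% dropout, so the intended margin over the typical 30% is almost absent.

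These figures assume that 197 is the 1:1 total, that the test is two-sided, that dropout is equal in the two arms, and that dropouts contribute no outcome information. They do not depend on the SD. That 1.45 was the multiplier is inferred from an exact match; the shortfall is there without it.

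**What to change.** Correct the Sample size paragraph with one of two statements:
- 321 participants maintain 90% power for dropout up to 31%; or
- at 45% dropout, power is about 82% (80% if a further 45% are lost after baseline from the 301 men with baseline data).

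Either way, note that 403 would have been needed for 90% power at 45% dropout, and say that the figure counts completers only.

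The cost is one sentence and a less favourable power statement. No recruitment, design or analysis change follows. The correction should be in place before the outcome results are interpreted.
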